**Table: Treatment, follow up and sample collection schedule *P.f*, *P. vivax* and mixed infections:**

| **Vivax Patients & Patients with mixed infection** | Day 0 | Day 1 | Day 2 | Day 3 | Day 4 | Day 5 | Day 6 | Day 7 | Day 8 | Day 9 | Day 10 | Day 11 | Day 12 | Day 13 | Day 14 | Day 15 | Day 16 | Day 23 | Day 30 | Un-scheduled visit |
| --- | --- | --- | --- | --- | --- | --- | --- | --- | --- | --- | --- | --- | --- | --- | --- | --- | --- | --- | --- | --- |
| FU P.f. patients | X | X | X | (x) |  |  |  |  |  |  |  |  | X |  |  |  | X | X | X |  |
| FU P.v. patients & mixed | X | X | X | (x) |  |  | X |  |  | X |  |  | X |  |  |  | X | X | X |  |
| Consent | X |  | X |  |  |  |  |  |  |  |  |  |  |  |  |  |  |  |  |  |
| Urinary Pregnancy testing (females, 13- 49years) | X |  |  |  |  |  |  |  |  |  |  |  |  |  |  |  |  |  |  |  |
| Capillary Finger Prick | X | X | X |  |  |  |  |  |  | X |  |  |  |  |  |  | X | X | X | X |
| Venous Blood Sample | X |  |  |  |  |  |  |  |  |  |  |  |  |  |  |  |  |  |  | X* |
| Microscopy | X | X | X | (X) |  |  | X |  |  | X |  |  | X |  |  |  | X | X | X | X |
| Hb | X | X | X | (X) |  |  | X |  |  | X |  |  | X |  |  |  | X | X** | X** | X |
| ACT treatment Pf and Pf/Pv | X | X | X |  |  |  |  |  |  |  |  |  |  |  |  |  |  |  |  |  |
| PQ treatment Pf |  |  |  | X |  |  |  |  |  |  |  |  |  |  |  |  |  |  |  |  |
| CQ treatment Pv | X | X | X |  |  |  |  |  |  |  |  |  |  |  |  |  |  |  |  |  |
| PQ treatment Pf and Pf/Pv |  |  |  | X | X | X | X | X | X | X | X | X | X | X | X | X | X |  |  |  |
| Masimo*** |  |  |  |  |  |  |  |  |  |  |  |  |  |  |  |  | X** |  |  | X |
| Pill count |  |  |  |  |  |  |  |  |  |  |  |  |  |  |  |  | X** |  |  |  |
| AE monitoring  *in case of recurrent parasitaemia  ** in Pv and Pf/Pv patients only  ***only in adults and children >2 yearsX | X | X | X |  |  |  |  |  |  | X |  |  |  |  |  |  | X | X | X | X |

## Concomitant treatment

Patients under regular medication at trial entry for conditions other than malaria, will have this documented on the CRF and will be asked to continue medication as usual. Any additional medications taken within the follow-up period must be documented in the CRF. Patients who prematurely discontinue trial medication, or who fail to respond to trial medication and receive other anti-malarial therapy will have this documented. Drugs with antimalarial activity should be avoided (Annex I).

## Rescue treatment

Treatment failure (see Annex VII) are treated according to national guidelines with quinine (Annex VI). This will be noted on the CRF. If the participant has started PQ treatment he will be asked to return for all scheduled follow up visits.

## Loss to follow up

Loss to follow-up occurs when, despite all reasonable efforts, an enrolled patient does not attend for the scheduled visits and cannot be found. Every effort will be made to schedule a follow-up visit for patients who fail to return.

## Patient withdrawal and protocol violation

- Withdrawal of consent. A patient may withdraw consent at any time, without prejudice for further follow-up or treatment at the study site.
- Protocol violation (e.g. enrolment violation or incomplete treatment). Patients with any protocol violation will be followed up as scheduled for safety assessment. This also includes patients with serious adverse events that necessitate termination of treatment before the full course is completed.

# Laboratory and test procedures

## Microscopy

Slides for microscopy will be collected upon enrolment and on all follow up days as well as on any unscheduled visit days.

All slides collected between day 0 and day3 will be re-read by an expert microscopists. Blood smears with discordant results (differences between the two microscopists regarding species diagnosis, parasite density of > 50% or regarding the positivity in general) will be re-examined by a third, independent microscopist, and parasite density will be calculated by averaging the two closest counts.

## RDT

Apart from microscopy all suspected malaria patients will be tested by Rapid Diagnostic Tests (RDT) on day 0. The trade name of the RDT that will be used in this study will be “FalciVax” which is produced by Zephyr Biomedicals, India. Each FalciVax is rapid self-performing, qualitative, two site sandwich immunoassay utilizing whole blood for the detection of *P. falciparum* specific histidine rich protein-2 (Pf, HRP-2) and *P. vivax* specific pLDH. RDT will be performed according to manufacturer instruction (<http://www.tulipgroup.com/Zephyr_New/qrg/falcivax.pdf>.

## Hemoglobin

. Haemoglobin (Hb) will also be measured at baseline and on all follow up visits using a Hemocue Hb (Angelholm, Sweden) machine.

## Serology

Additional serological tests to detect the malaria parasite as well as to assess the response of the host towards the parasite will be performed on collected venous blood at the study laboratory or a reference centre.

## Enzyme activity testing

G6PD activity will be measured using spectrophotometry at the lab maintained by icddr,b for all participants. Samples are transported on a daily basis from the field to the icddr,b lab and results are communicated to the field. A subset of collected samples, tested with spectrophotometry, will be tested with flow cytometry to assess lyonisation at a reference centre capable of performing the respective procedure

## Methhemoglobin

Methemoglobin will be measured by non-invasive methods (Masimo) in vivax patients to determine adherence to unsupervised primaquine treatment

## Molecular testing (parasite)

Parasite DNA will be collected on day 0 and any recurrent parasitaemia. Parasite DNA will be extracted for sequencing and genotyping of the parasite to detect markers of resistance. Molecular testing will be done at the Sanger Institute, UK through Menzies.

## Molecular testing (host)

Based on availability of funds a subset of samples will be tested for known and unknown variants of the G6PD gene. Genotyping and sequencing will be done at the Sanger Insitute, Uk. Host genotyping is strictly related to the G6PD gene (Xq28) and only to achieve the study objectives.

# Assessment of variables and statistical methodology

## Safety endpoints

- Proportion of patients with severe anaemia (Hb<7g/dl)
- Proportion of patients receiving blood transfusion
- Fractional change in Hb between baseline and day 6, 9,12,16, 23 and 30 (incl. proportion of patients with >25% drop in Hb between the timepoints)
- Proportion of patients with anaemia less than 7g/dl on day 3 and day 9
- Proportion of patients with adverse and serious adverse events

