# Statistical analyses

- Safety data will be presented as summary statistics (including number, mean, median, interquartile range, standard deviation, minimum and maximum) of all vital signs variables (values and changes from baseline) will be calculated for each visit by treatment group.
- G6PD activity will be categorised and the relative risk (RR) of a drop of Hb > 25% between day 3 and 9 and day 3 and 16 and day 23 and 30 will be calculated per category for all participants treated with 14 days of PQ.
- Hematological results will be presented as continuous variable of Hb concentration at Day 0, 3, 6, 9, 12 and 16. The fractional fall in Hb between baseline and day 9 and 16, will be calculated, as well as the proportion of patients with anaemia less than 7g/dl between day 3 and day 9.
- Parasite clearance rate will be defined according to the World Wide Antimalarial Resistance Network guidelines (WWARN)[[20](#_ENREF_20)]. The parasite clearance time (PCT) is defined as the time elapsed between the patient’s first dose and the time of the first negative blood slide.
- G6PD variants detected will be presented descriptively, G6PD activity observed will be displayed in the form of a histogram displaying G6PD activity vs. number of patients.

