**SYMPTOM REPORTING FORM - Page 1**

| **Type of AE**  **(one per row only)** | **Onset Date** | **Severity Grade**  **(check one)** | **Actions Taken?**  **(specify below if needed)** | **Is AE related to PQ?**  **(check one)** | **Date Resolved** | **Outcome of AE (check one)** |
| --- | --- | --- | --- | --- | --- | --- |
| ☐Rash  ☐Nausea  ☐Vomiting  ☐Abdominal pain  ☐Dark Urine  Hillmen index: _ _  ☐Diarrhea  ☐Poor appetite  ☐Other (describe): _________________ | _ _ / _ _ / _ _ | ☐ Mild  ☐ Moderate  ☐Severe  ☐ Life-threatening | ☐ None  ☐ Stopped PQ  ☐ Prescribed drug  ☐ Blood Transfusion  ☐ Hospitalization  ☐ Other** | ☐ Unrelated  ☐ Unlikely  ☐ Possible  ☐ Probable  ☐ Definite | _ _ / _ _ / _ _  or ongoing ☐ | ☐ Recovered/resolved  ☐ Recovered/resolved with sequelae  ☐ Recovering/resolving  ☐ Not recovered/not resolved  ☐ Fatal  ☐ Unknown |
| ☐Rash  ☐Nausea  ☐Vomiting  ☐Abdominal pain  ☐Dark Urine  Hillmen index: _ _  ☐Diarrhea  ☐Poor appetite  ☐Other (describe): _________________ | _ _ / _ _ / _ _ | ☐ Mild  ☐ Moderate  ☐Severe  ☐ Life-threatening | ☐ None  ☐ Stopped PQ  ☐ Prescribed drug  ☐ Blood Transfusion  ☐ Hospitalization  ☐ Other** | ☐ Unrelated  ☐ Unlikely  ☐ Possible  ☐ Probable  ☐ Definite | _ _ / _ _ / _ _  or ongoing ☐ | ☐ Recovered/resolved  ☐ Recovered/resolved with sequelae  ☐ Recovering/resolving  ☐ Not recovered/not resolved  ☐ Fatal  ☐ Unknown |
| **Definitions**  Severity – Mild (easily tolerated; no or minimal interference with daily activities); Moderate (low level of inconvenience; greater than minimal interference with daily activities); Severe (interrupts normal daily activities; usually incapacitating); Life-threatening (life-threatening consequences; urgent intervention indicated); Fatal (death) | | | | | | |

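### The >25% Hb-fall endpoint and its relative risk by G6PD category rest on scheduled-day values, so a haemolysis transfused between visits can be scored as no event

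*Protocol*

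**What the plan says.** Protocol section 5.1 (Safety endpoints) defines the continuous endpoint as "Fractional change in Hb between baseline and day 6, 9,12,16, 23 and 30" and attaches the binary one to it: "incl. proportion of patients with >25% drop in Hb between the timepoints". The synopsis gives a shorter list (days 9, 16, 23 and 30). Both lists name scheduled days only.

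Section 7 (Statistical analyses) plans, per G6PD category and for everyone given 14 days of PQ, the relative risk of "a drop of Hb > 25% between day 3 and 9 and day 3 and 16 and day 23 and 30". It specifies no other risk by G6PD category.

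Section 5.1 lists transfusion separately, as "Proportion of patients receiving blood transfusion", and severe anaemia (Hb below 7 g/dl) with no visit day attached.

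The study collects more than these endpoints use. The schedule table in section 4.4.1 and the case record form in Annex IX provide for Hb at unscheduled visits. The symptom form in Annex IX offers "Blood Transfusion" as an action taken, with onset and resolution dates for the event but no date for the transfusion.

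On patients who receive rescue treatment, section 4.4.3 says: "If the participant has started PQ treatment he will be asked to return for all scheduled follow up visits".

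**The concern.** Transfusion raises Hb directly. If a patient haemolyses, attends unscheduled and is transfused, the low value is taken on a day the endpoint does not name, and the value on the next named day includes donor cells. Scored from the named days alone, the patient may show no fall above 25%.

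The cases at risk of being lost are the most severe ones. They would be lost from the analysis that serves the secondary objective on haemolysis risk and G6PD activity. If they occur mainly in patients with lower G6PD activity, the relative risk is pulled towards 1.

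**Working it through.** The protocol states no event rate, transfusion rate or effect size, so there is no planned figure to reproduce. The check has three parts.

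**1. Can a transfusion hide the fall?** Let R be the reference Hb (baseline in section 5.1; day 3 for the first two windows of section 7) and V the Hb on the named day. The fall is (R − V)/R, and it stops being an event once V reaches 0.75R. From a nadir N, the net rise needed to hide it is 0.75R − N. With assumed values in g/dl:

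| R | N | Fall at N | Net rise that hides it |
|---|---|---|---|
| 10 | 6.9 | 3.1/10 = 31% | 7.5 − 6.9 = 0.6 |
| 12 | 6.9 | 5.1/12 = 42.5% | 9.0 − 6.9 = 2.1 |
| 14 | 6.9 | 7.1/14 = 50.7% | 10.5 − 6.9 = 3.6 |

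A worked case: R = 11.0, unscheduled Hb 6.5 (4.5/11.0 = 41%), transfused, next scheduled Hb 9.0 (2.0/11.0 = 18%). No event is scored. Hiding is therefore possible but not automatic; it is harder from a high reference value.

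**2. How long are the gaps?** On the section 5.1 list, vivax and mixed patients have Hb on days 6, 9, 12 and 16 during PQ, so gaps are 3 or 4 days; afterwards (days 23 and 30) they are 7 days. If the section 7 windows compare only their two end values, the gaps are 9 − 3 = 6 days, 16 − 3 = 13 days and 30 − 23 = 7 days, and even the scheduled day 6 and day 12 values drop out.

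**3. What does one case do?** Section 8 targets about 50 vivax patients, which I use as an approximate denominator. Mixed infections also receive 14 days of PQ but have no stated target, and severely G6PD-deficient patients receive none.

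- Proportion: 1/50 = 2.0 points per case. For scale, the exact 95% confidence interval at 2/50 is 0.5% to 13.7%.
- Relative risk, illustration only. The split takes the 20–40% G6PD deficiency range from the Rationale; the event counts (3 low-activity, 2 normal) are assumed.
  - 10 low, 40 normal: (3/10)/(2/40) = 6.0. One low-activity case hidden: (2/10)/(2/40) = 4.0.
  - 20 low, 30 normal: (3/20)/(2/30) = 2.25. One low-activity case hidden: (2/20)/(2/30) = 1.5.
  - If the hidden case is in the normal group instead, the relative risk rises: (3/10)/(1/40) = 12.0, or (3/20)/(1/30) = 4.5.

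The direction thus depends on where the case falls. A bias towards 1 assumes that transfused haemolysis is commoner with low activity.

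**The case against.** The strongest reply is that handling of values after transfusion or rescue commonly sits in a statistical analysis plan, which may exist and is not shown. That is fair for the details. But the protocol has itself fixed the days, the windows and the all-treated population, and taken literally those choices can misclassify a case.

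Second, *between* in sections 5.1 and 7 could be read as any value in the interval, which would admit unscheduled Hb. The wording allows this, but only scheduled days are named, so the intended reading has to be stated.

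Third, the case is not lost from the safety results. It stays in the transfusion and undated severe-anaemia endpoints, and since G6PD activity is measured in everyone, transfusions could be tabulated by category. This stands: the loss is confined to the >25% fall and its relative risk.

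Fourth, severely deficient patients receive no PQ, which makes the scenario less likely, and with five events any single change moves the ratio a lot. Both stand and limit the size. The pooling across sites planned in section 8 for the primary objective improves precision but does not correct misclassification.

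A reader might also infer that a fall after recurrent malaria is counted as PQ-related. The documents do not say so. The Hb endpoint assigns no cause, relatedness is recorded only for adverse events on the symptom form, and recurrence is its own endpoint. Continuing follow-up after rescue is a legitimate all-follow-up approach. It is true only that falls before and after recurrence are not shown apart; the day 23 to 30 window, which opens a week after the last PQ dose on day 16, is where this matters most.

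**Conclusion.** The point holds in a limited form. As written, the >25% Hb-fall endpoint and its relative risk by G6PD category do not use the unscheduled Hb or the transfusion record, so a transfused haemolysis can be scored as no event in the only analysis section 7 specifies by G6PD category.

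Each such case is worth about 2 points in the vivax proportion, which is small beside the sampling error at 50 patients. It can shift the relative risk materially, but those figures rest on assumed counts and should be read only as an illustration. How many cases will arise cannot be derived from the protocol. The change is still worth making before analysis because the misclassification would fall on the most severe events and the remedy is cheap.

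**What to change.** In sections 5.1 and 7, state that:

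- (a) Hb from unscheduled visits within a window counts towards the >25% fall and the <7 g/dl endpoints. Say also whether the scheduled day 6 and day 12 values count in the section 7 windows.
- (b) A patient transfused after PQ starts counts as an event for the >25% fall and the relative risk. List transfusions given for reasons other than haemolysis individually and add a sensitivity analysis that excludes them. The windows leave days 17 to 22 uncovered, so say where a transfusion then is counted.
- (c) In the continuous Hb summaries, post-transfusion values are flagged and results are given with and without them. The nadir is not carried forward to later visits, because that would misstate recovery.
- (d) The all-follow-up analysis stays as it is, with a supportive table of falls before and after recurrence or rescue treatment.

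Cost: analysis wording plus one new field, the transfusion date, on the Annex IX symptom form. The downside is that a few transfusions not due to haemolysis may count as events; the listing and sensitivity analysis in (b) make that visible. Clinical management does not change.

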# Objective

**Primary:**

- To assess side effects observed following unsupervised PQ treatment in *P. vivax* and *P. falciparum* patients

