**Table: Maximum amount of venous blood collected on d0 / body weight**

| **Patient’s approximate weight in kilograms** | **Amount (mL)** |
| --- | --- |
| >6 to 7 | 4-5 |
| >7 | 5 |

All participants will be followed daily until day 2 to provide supervised treatment and ensure clinical and parasitological recovery following chloroquine (Pv arm) or artemether-lumefantrine (Pf arm and Pf/Pv arm) treatment.

Thereafter patients (excluding those with severe G6PD deficiency) will be given unsupervised primaquine for 1 dose (Pf arm) or 14 doses (Pv/mix arm) and reviewed again after 7 days (day 9), 14 days (day 16), 21 days (day 23) and 28 days (day 30). All P. vivax and mixed infections will in addition be followed up after 3 and 10 days (day 6 and 12 respectively) to assure the safety of the provided treatment. Any patient developing signs and symptoms indicative of a malarial episode or an adverse event within the follow up period will be asked to re-attend the clinic for an unscheduled visit, where they will be offered clinical management according to local clinic guidelines. A fingerprick will be performed during every follow up and unscheduled visit, 5ml of blood will be collected for every recurring malaria episode (see table below). Information on adverse events will be collected during every visit. Whenever possible a pill count will be performed on day 16.

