***If no***

Principal reason for premature termination:

☐Patient vomited the study drug a second time and received rescue treatment before PQ was given

☐Early Treatment failure before PQ was given

☐Patient found to be severely G6PD deficient and excluded before PQ treatment was given

☐Patient withdrew consent

☐Lost to follow up

☐Death

☐ Other: please specify………………………………………………

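### Three of the five safety endpoints (AEs/SAEs, severe anaemia, transfusion) are not tied to primaquine start or to primaquine recipients, although the primary objective is side effects following primaquine

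*Protocol*

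**What the plan says.** The primary objective (section 3) reads "To assess side effects observed following unsupervised PQ treatment in", and names both infections, vivax and falciparum. Section 4.4.1 and Annex V start PQ on day 3 in all groups: one dose in falciparum, 14 days in vivax and mixed infections.

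Section 5.1 lists five safety endpoints:

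- severe anaemia, meaning Hb below 7 g/dL
- need for a transfusion
- Hb change over time, worded as "Fractional change in Hb between baseline and day 6, 9,12,16, 23 and 30", together with the share whose Hb falls by more than a quarter
- Hb under 7 g/dL at the day 3 and day 9 assessments
- AEs and SAEs, worded as "Proportion of patients with adverse and serious adverse events"

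None of them mentions PQ. The first, second and fifth have no time window, and they appear in the synopsis in the same open form.

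On collection, section 4.4 says "Information on adverse events will be collected during every visit". The schedule table marks adverse-event (AE) monitoring on days 0, 1, 2, 9, 16, 23 and 30 and at unscheduled visits. It marks Hb from day 0 onwards.

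Some enrolled patients never receive PQ. The end-of-study form in Annex IX lists "Patient found to be severely G6PD deficient and excluded before PQ treatment was given", and also early treatment failure and a second vomiting episode with rescue treatment, each before PQ.

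**The concern.** On days 0 to 2 every patient has acute malaria and is taking CQ or AL. The symptom form lists nausea, vomiting, abdominal pain, diarrhoea and poor appetite, all of which can come from the infection or from those drugs. An endpoint with no start point counts vomiting on day 1 the same way as an event in the first week of PQ.

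The result would be a proportion that answers a broader question than the primary objective asks. Section 8 plans to pool the primary-objective results with other sites, so the mixture would carry into the pooled figure. The Hb-change endpoint has a related fault: its assessment days follow PQ start, but its reference value is from day 0.

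**Working it through.** **Step 1. Each endpoint against PQ start on day 3**

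| Endpoint (section 5.1) | Can count events on days 0 to 2? | Names PQ recipients? |
| --- | --- | --- |
| AEs/SAEs | Yes, no window | No |
| Severe anaemia, Hb below 7 g/dL | Yes, no window | No |
| Transfusion | Yes, no window | No |
| Fractional Hb change | No (days 6 to 30), but measured from day 0 | No |
| Anaemia on days 3 and 9 | No | No |

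Three of the five can count events before PQ, and none of the five names a PQ-treated denominator. Of the seven scheduled days in the AE row, three (0, 1, 2) precede PQ.

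**Step 2. Where the gap matters most.** Section 4.3 excludes acute anaemia below 8 g/dL at entry. Severe anaemia before PQ therefore needs a fall from at least 8 to below 7 g/dL by day 2. No such limit applies to AEs, so the AE/SAE endpoint is the most exposed.

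**Step 3. Illustration for the AE endpoint.** The protocol states no event rates, so every input here is an assumption. Let q be the risk of an event on days 0 to 2, p the risk after PQ start among recipients, and s the share never given PQ. With independent risks, and all enrolled patients counted:

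observed = (1 − s) × [1 − (1 − q)(1 − p)] + s × q

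| q | p (target) | s | Calculation | Observed |
| --- | --- | --- | --- | --- |
| 5% | 5% | 5% | 0.95 × 0.0975 + 0.05 × 0.05 | 9.5% |
| 10% | 5% | 5% | 0.95 × 0.145 + 0.05 × 0.10 | 14.3% |
| 30% | 5% | 15% | 0.85 × 0.335 + 0.15 × 0.30 | 33.0% |

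In the middle row, patients with a pre-PQ event make up 0.10 / 0.143 = 70% of those counted.

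**Step 4. Denominator alone.** With no pre-PQ events (q = 0) the formula reduces to (1 − s) × p. For an assumed s of 5% to 20%, a true 5% reads 4.75% to 4.0%. Section 2 gives 20-40% for G6PD deficiency but no severe share, so s cannot be taken from the document. Within this range the effect is small beside the window effect.

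**Step 5. Day-0 reference for Hb.** If Hb falls by a fraction f before PQ, the further fall needed to reach 25% from day 0 is 1 − 0.75/(1 − f):

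| Fall before PQ (assumed) | Further fall that reaches 25% in total |
| --- | --- |
| 5% | 21.1% |
| 10% | 16.7% |
| 15% | 11.8% |
| 20% | 6.25% |

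**Step 6. Does section 7 already solve this?** It plans a relative risk of an Hb fall above 25% from day 3 to days 9 and 16, in participants treated with 14 days of PQ, by G6PD category. That analysis is tied to PQ, but it covers Hb only and omits the single-dose group, about 160 of the 210 patients targeted. Its day-3 reference is also insecure: section 4.4 follows patients daily only to day 2, the schedule puts day-3 Hb in brackets, and the case record form goes from Day 2 to Day 6.

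**The case against.** The strongest reply is that a safety population and a treatment-emergent window are usually set in the statistical analysis plan, which is not at hand. That would hold if the protocol were silent on such matters throughout. It is not. Section 5.2 gives days and a 30-day limit and restricts one endpoint to falciparum patients, section 5.3 restricts another to the vivax cohort, and section 7 restricts an analysis to 14-day PQ recipients. Where the protocol wants a window or population, it states one.

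A second reply has more force. Sections 2 and 4.1 describe the safety of routine treatment under the national guidelines as a whole, so reporting events under CQ and AL has a legitimate basis. The mismatch is with the narrower primary objective. This is a reason to keep the early events as a separate row, not to leave them merged.

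Some stronger readings are tempting but not supported:

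- *The safety endpoints do not measure PQ side effects at all.* They measure a mixture, and two of the five count nothing on days 0 to 2.
- *The denominator is all enrolled patients.* The protocol does not say so. It leaves the denominator undefined.
- *Nothing but the relatedness tick box links events to PQ.* Section 7 contains the day-3 Hb analysis, and the forms record onset date, whether PQ was stopped and whether PQ was provided.
- *Early symptoms cannot be separated.* The Day 0 page has no symptom checklist, but AE monitoring is scheduled from day 0 and each AE row carries an onset date.

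**Conclusion.** The point holds for AEs/SAEs, severe anaemia and transfusion: as written, they are tied neither to PQ start nor to PQ recipients, while the primary objective is. It matters most for AEs/SAEs. The Hb-change endpoint has the lesser fault of a day-0 reference. The undefined place of patients never given PQ is a real gap with a small effect over the range considered.

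The size cannot be derived from the protocol. The 14% against 5% rests on assumed risks, on independence between the two periods and on all enrolled patients being counted; it shows direction and plausible scale only. The study is descriptive and the data needed to separate the periods are collected, so this is a correction of definitions and not a flaw in the design.

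**What to change.** In section 5.1 and the synopsis:

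- Define the AE/SAE, severe-anaemia and transfusion endpoints among patients given PQ, counting events with onset or worsening from PQ start. A worsening should be entered as a new row with its own date. Transfusion is recorded as an action on an AE row and can be dated through it.
- Add an Hb change measured from the last value before PQ: day 2, or day 3 where it is taken.
- Report single-dose (falciparum) and 14-day (vivax, mixed) recipients separately.
- Report day 0 to 2 events, and events in patients not given PQ, as separate background rows.
- State that exposure means PQ provided (item 19 of the case record form). Intake is unsupervised, and the schedule limits pill count and Masimo to vivax and mixed patients, so neither checks the single falciparum dose.

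Onset date, Hb by visit and PQ provision are already collected, so no new data are needed. The cost is a wording change and a slightly smaller denominator.
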